#### 4.4 Contraindications to repeated vaccination

The following adverse events constitute absolute contraindications to further administration of PEV 301 / PEV 302; if any of these adverse events occur during the study, the subject must not receive additional doses of vaccine but may continue other study procedures at the discretion of the investigator. The subject must be followed until resolution of the event, as with any adverse event (see Section 8):

- Anaphylactic reaction following the administration of vaccine(s).
- Any clinically relevant immunosuppressive or immunodeficient condition

The following adverse events constitute contraindications to administration of PEV 301 / PEV 302 at that point in time; if any one of these adverse events occurs at the time scheduled for vaccination, the subject may be vaccinated at a later date, within the time window specified in the protocol (see Schedule of Assessments Page 8), or withdrawn at the discretion of the investigator. The subject must be followed as with any adverse event (see Section 8).

- Acute disease at the time of vaccination. (Acute disease is defined as the presence of a moderate or severe illness with or without fever. All vaccines can be administered to persons with a minor illness such as diarrhea, mild upper respiratory infection with or without low-grade febrile illness, i.e., temperature  $<38^{\circ}\text{C}$ ).
- Temperature  $\geq 38^{\circ}\text{C}$  at the time of vaccination.

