## 1.5 Benefits and Risks

Volunteers will not benefit directly from participation in this study. However, it is hoped that the information gained from this study will contribute to the development of a safe and effective malaria vaccine. The general risks to participants in this Phase I study are associated with phlebotomy and with vaccination. The volume of blood drawn over the study should not compromise these otherwise healthy subjects. Potential risks include the following:

**Local reactions:** Mild tenderness, bruising, or fainting may result from venipuncture. An inflammatory reaction as manifested by redness, swelling, and/or tenderness may occur at the site of vaccine injection. All these local reactions have spontaneously resolved within weeks.

**Systemic Reactions:** Systemic reactions to immunization could theoretically occur, and include a flu-like illness with low-grade fever, chills and malaise. However, experience to date with other CSP vaccines suggests that if such reactions occur, they resolve in 12 days without therapy or limitation of daily activity. Serum sickness reactions due to deposition of antigen-antibody complexes, or idiosyncratic immune responses not dependent on immune complexes could theoretically develop resulting in damage to organs, such as the liver or kidney. Such immunemediated reactions have not been reported to date after malaria vaccines. Temporary ascending paralysis, the Guillain-Barré syndrome, may occur with any vaccine, although it is very rare.

**Allergic Reactions and Anaphylaxis:** As with any vaccine, allergic reactions are possible. A variety of synthetic and recombinant malaria peptide vaccines have induced systemic allergic responses, e.g., urticaria and anaphylaxis. The allergic reactions occurred after 2-3 vaccinations administered at intervals of 1 month or more, vaccines were formulated with Alhydrogel or QS-21 adjuvants, and high antigen concentrations (200 µg - 2000 µg) were inoculated with each dose. Reactions were occasionally associated with development of antigen-specific IgE antibody.

**Adventitious Agents:** Each lot of vaccine is tested for sterility and for either endotoxin content or pyrogenicity. The formulated product is released for use in humans when the release criteria are met, which suggests that the product is free of known microbial contamination that could infect humans. Nevertheless, the risk of unknown microbe is always present.

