### 9.4 Data and Safety Monitoring Board

A Data and Safety Monitoring Board (DSMB) will be established if one of the following situations occurs:

- One or more subjects experienced a serious adverse reaction assessed as related to the vaccine by the investigator
- One or more subjects experienced anaphylaxis
- Two or more subjects in a single dose and antigen cohort experienced a severe adverse event not explained by a diagnosis unrelated to vaccination. (For grading of severity see Appendix 4)

The DSMB will then analyze the data and decide on the continuation of the study.

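### Section 4.4 does not bar the next dose for a volunteer who has recovered from a vaccine-related serious reaction, or from a systemic allergic reaction short of anaphylaxis

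*Protocol*

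**What the plan says.** Section 4.4 has two lists. The first is permanent: "The following adverse events constitute absolute contraindications to further administration of PEV 301 / PEV 302". It contains anaphylaxis after vaccination and clinically relevant immune deficiency or suppression. The second is temporary and covers acute moderate or severe illness and a temperature of 38 °C or more: "if any one of these adverse events occurs at the time scheduled for vaccination, the subject may be vaccinated at a later date". The option in that sentence for the investigator to withdraw the volunteer belongs to this second list only. Section 8.10 separately bars further doses in pregnancy.

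Section 9.4 sets up a safety board on any of three triggers. One is a case of anaphylaxis. The others are "One or more subjects experienced a serious adverse reaction assessed as related to the vaccine by the investigator" and "Two or more subjects in a single dose and antigen cohort experienced a severe adverse event not explained by a diagnosis unrelated to vaccination". Its task is then stated: "The DSMB will then analyze the data and decide on the continuation of the study".

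Section 1.5 describes the class hazard: "A variety of synthetic and recombinant malaria peptide vaccines have induced systemic allergic responses, e.g., urticaria and anaphylaxis". It adds: "The allergic reactions occurred after 2-3 vaccinations administered at intervals of 1 month or more", and "Reactions were occasionally associated with development of antigen-specific IgE antibody".

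**The concern.** Section 8.3.1 says these products have not been given to humans before, and section 1.5 says volunteers gain no direct benefit. Nothing on the volunteer's side offsets the risk of a further dose after a serious or systemic allergic reaction to an earlier one.

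The temporary list looks only at the volunteer's state on the dosing day, and the gap between doses is about two months or longer. A reaction that has settled by then is outside both lists. Section 4.4 thus leaves out an event type that section 1.5 names as a hazard of repeated malaria peptide vaccination (urticaria). It also leaves out one that section 9.4 ranks with anaphylaxis as a single-case trigger (a related serious reaction).

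There is a parallel mismatch with entry. Exclusion criterion 9 in section 4.3 refuses a volunteer whose allergic history makes a vaccine component risky, but it is checked at study entry. No equivalent is stated before doses 2 and 3 for someone who has since reacted to the vaccine itself.

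**Working it through.** **Step 1. Each type of event against each rule.** The events are taken as resolved before the next dose, except in the last row.

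| Event in one volunteer | Barred by 4.4? | Triggers the 9.4 board? |
|---|---|---|
| Anaphylaxis | Yes | Yes, one case |
| Related serious reaction, not anaphylaxis | No | Yes, one case |
| Non-serious systemic allergic reaction, e.g. urticaria | No | No |
| Acute illness or fever on the dosing day | Deferred, or withdrawn if the investigator so decides | Not in itself |

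In the second row the board rules on the study, and section 9.4 gives no rule for that volunteer's own next dose. In the third row the only remaining trigger is the one for severe events, and it needs at least two volunteers in one dose and antigen cohort.

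**Step 2. How much of the allergic spectrum is left uncovered.** Section 8.1 gives allergic bronchospasm needing intensive treatment as an example of a serious event. If related, it sits in the second row and reaches the board. What remains in the third row is mainly non-serious urticaria and similar reactions.

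**Step 3. Time for a reaction to settle before the next dosing-day check.**

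- Windows in 5.2.2 (day 1; 57–66; 176–187): dose 1 to 2 is 57 − 1 = 56 to 66 − 1 = 65 days; dose 2 to 3 is 176 − 66 = 110 to 187 − 57 = 130 days.
- Windows in section 3 (day 1; 64–66; 183–185): dose 1 to 2 is 64 − 1 = 63 to 66 − 1 = 65 days; dose 2 to 3 is 183 − 66 = 117 to 185 − 64 = 121 days.

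On either set of windows, a transient reaction can be over before the temporary list is applied.

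**Step 4. Number of doses governed by the rule.** Five active groups of 8 give 5 × 8 = 40 volunteers. Doses 2 and 3 give 40 × 2 = 80 repeat active doses at most. Section 1.5 places the allergic reactions after the second or third vaccination. On that pattern, a reaction after dose 3 has no later dose to bar, and one after dose 2 leaves only dose 3. The relevant ceiling is then 40 × 1 = 40 doses, and fewer if a group stops after dose 2 under section 10.8.

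**Step 5. How far the history in 1.5 carries over.** Those reactions came with other adjuvants and 200–2000 µg of antigen per dose, against 10 or 50 µg per antigen here. The ratio runs from 200 / 50 = 4 to 2000 / 10 = 200.

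**The case against.** The best case against is that section 4.4 sets a minimum and leaves the rest to the physician, with ample opportunity to act:

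- The Synopsis (Procedure) has the investigator assess safety before the second and third immunizations, check health status before each dose, and take chemistry and hematology.
- Section 8.3 has all adverse events evaluated at every visit, so a reaction should be on record well before the next dose.
- Section 9.2 lists adverse events as a reason for drop-out, and section 12.4 pays in full a volunteer who has to leave for that reason.
- Section 8.8 requires a serious event to be reported within one calendar day. A board convened because of one volunteer would hardly overlook that volunteer's next dose.
- Section 12.9 allows the sponsor to stop the study for safety, and Appendix 1 carries a general duty to discontinue research that may harm the individual.

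All of this stands as mitigation. Re-dosing after a known reaction would have to be a deliberate decision. None of it, however, states when an individual must receive no further dose.

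Two limits on the argument from section 1.5 also stand. A bar that needs a prior reaction cannot prevent a first reaction at dose 2 or 3. And section 1.5 does not say that urticaria came before anaphylaxis or grew worse with further doses.

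A reader might infer that the protocol requires such a volunteer to be dosed, or that nothing would stop it. The text does not support that: being absent from the list is not an order to vaccinate, and the safeguards above are real. Nor does it support treating all 80 repeat doses as carrying the pattern in section 1.5.

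**Conclusion.** The gap is real but small. As written, section 4.4 does not bar the next dose for a volunteer who has recovered from a related serious reaction or from a non-serious systemic allergic reaction. The first case is largely contained in practice by the board. The second, in a single volunteer, meets neither a bar nor a trigger and is the main reason to act.

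The number of volunteers affected cannot be estimated from the protocol. It should be low: section 10.7.1 expects no attributable serious event, and the antigen doses are well below those in section 1.5. The ceiling is 80 repeat active doses, and mainly the 40 third doses.

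The conclusion assumes that the lists in 4.4 and 8.10 are the complete set of mandatory individual bars; no other section of the protocol states one. No analysis or trial conclusion depends on the point. It concerns volunteer protection, and a dosing rule belongs in the protocol itself. The change is recommended because it is cheap.

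**What to change.** Add two items to the permanent list in section 4.4:

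- (a) Any serious adverse event that the investigator, on individual assessment, judges related, probably related or possibly related to the vaccine. State that an event does not qualify merely because it falls in the 4-day solicited period. Sections 8.3.1 and 8.5 together deem every solicited reaction related, and without this wording a coincidental serious event in those days could bar a volunteer for good.
- (b) Any systemic allergic reaction attributed to the vaccine, such as generalised urticaria or bronchospasm. Local injection-site reactions do not count.

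Add one sentence: at the assessment already required before doses 2 and 3, the investigator checks the recorded adverse events against this list. The temporary list stays as it is.

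This needs no new visit or blood sample. The cost is that an affected volunteer misses a dose. One who misses dose 2 leaves the per-protocol immunogenicity set under section 10.9, taking that group from 8 to 7 (1/8 = 12.5%). One who misses only dose 3 still meets the second-dose criterion. In both cases the volunteer can remain in follow-up under section 4.4 and stays in the safety population, so the primary objective keeps the data.

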## 5 Conduct of study

### 5.1 General study aspects

The clinical part of the study will be conducted at the Clinical Research Centre of the Kantonsspital Basel. PD [name] is the Clinical Investigator.

It is the investigator's responsibility to ensure that the intervals between visits/contacts are strictly followed. These intervals during the active phase of the study determine a subject's evaluability in the as per protocol analyses.

## 5.2 Detailed description of study stages/visits

For information on time points of visits, vaccinations & checks refer to schedule of assessments page 8.

### 5.2.1 Screening of potential study participants

During the Screening Visit (days –7 to -5) the investigator has to check whether potential participants for this study meet the inclusion criteria. Volunteers will not be included if any of the exclusion criteria apply. Volunteers who have signed the Informed Consent Form will undergo complete physical examinations, including vitals signs (blood pressure, pulse, temperature) and body systems (cardiovascular, gastro-intestinal, CNS, ENT, respiratory, urogenital, dermatology). Demographic data will be collected, and a complete clinical history will be recorded, and laboratory tests (including HIV and influenza A titer) and a pregnancy test in female volunteers will be performed. In the event that a subject is tested positive for HIV, he/she will be informed and referred for counseling and treatment. Temperature will also be measured daily by the subject and recorded on the diary card provided.

If materials are provided by a centralized laboratory, it is mandatory that all clinical samples (including serum samples) be collected using exclusively those materials in the appropriate manner. The use of other materials could result in the exclusion of the subject from analysis. The investigator must ensure that his/her personnel and the laboratory(s) under his/her supervision comply with this requirement.

### 5.2.2 Vaccinations

Volunteers will be vaccinated on days 1, 64 (57 – 66) and 183 (176 – 187) respectively. The 3rd vaccination will not be applied, if 3 weeks after the 2nd vaccination no immune response is seen.

Prior to the vaccination the baseline AE rate has to be assessed by the investigator.

### 5.2.3 Follow-up visits

For timepoints see schedule of assessments, page 8

Study participants have to report to the study site 48 hours, i.e. on day 2 (+1) after each vaccination. If a visible local reaction occurs, the investigator has to take a picture of the injection site. He has to record any adverse events in the CRF. The investigator has to check whether the study participants fill in the diary card provided to them.

The second follow-up visit has to be performed 7 (+2) days after each vaccination. The investigator has to collect the diary card, to record any adverse events not recorded by the participant and to take blood samples for safety checks (see 5.3.4.)

The 3rd follow-up visit has to be made 22 (+5) days after each vaccination. The investigator has to assess the health status of the participant and to take blood samples for safety and immunology tests (see 5.3.4.)

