| SAFETY                         |                                                   | 
 
Occurrence of adverse events: self-assessment of local and systemic reactions for 4 days after each vaccination (diary) as well as assessment by investigator during 30 minutes after each vaccination and 2 (+1) days as well as 7 (+2) days after each vaccination.
 
Occurrence of clinically significant hematological and biochemical abnormalities (hematological and biochemical analysis will be carried out at the screening visit (baseline), 7 (+2) and 21 (+5) days after each vaccination).
 
Significant reduction of health status compared to baseline (as assessed by investigator at baseline, i.e. prior to 1st vaccination, during 30 minutes after each vaccination and 21 (+5) days after each vaccination).
 
                                                                                                                                                                                                                                                                                                                                                                                                                                                                                                                                                                                                                                                                                                                                                                                                                                                                                                                                        |

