| PROCEDURE                                  | 
Volunteers will be screened, enrolled and followed by the clinical investigator, PD [name] at the Clinical Research Centre of the Kantonsspital Basel.
 
At the screening-visit (days -7 to -5) and after written informed consent has been obtained, the eligible healthy subjects are randomized to vaccination with either three injections of PEV 301 10 µg (Group A) or PEV 302 10 µg (Group B) or PEV 301 50 µg (Group C) or PEV 302 50 µg (Group D) or PEV 301 50 µg plus PEV 302 50 µg (Group E) or virosomes alone (group F) at days 1(+2), 64(+2) and 183(+2).
 
If possible 23 men and 23 women should be enrolled; however, if it is not possible to have an equal sex distribution, the groups can be filled with participants of either sex.
 
The 18 volunteers recruited in October will first be stratified into males and females and then randomized in blocks of 9 (1 block = females, 1 block = males) into 3 groups: Group A (n= 8) will be vaccinated with 10 µg PEV 301, Group B (n = 8) will be vaccinated with 10µg PEV 302, and 2 volunteers will receive virosomes alone (Group F) 5 weeks later again 18 volunteers have to be recruited, they first will be stratified into males and females and then randomized into 3 groups: group C (n = 8) will be vaccinated with 50 µg PEV 301, group D (n = 8) with 50 µg PEV 302, and 2 volunteers will receive virosomes alone (Group F).
 
5 weeks after the 2nd vaccination of groups C and D 10 volunteers will be randomized in blocks of 5 to either group E (n = 8) receiving the combination of 50 µg PEV 301 plus 50 µg PEV 302 or group F (n = 2) receiving virosomes alone.
 
Immunogenicity assessments for humoral immune response are made at baseline (screening blood sample on days -7 to -5), on the days of the 2nd and 3rd vaccination (pre-vaccination samples) as well as 21 (+5) days after each vaccination.
 
Cell mediated immune response will be assessed in groups C, D, E and F only, at baseline (during screening), and 21 (+5) days after each vaccination.
 
Safety assessments are made by the investigator at baseline (before the 1st immunization) and before the 2nd and 3rd immunization as well as 2 (+1) and 7 (+2) days after each immunization.
 
After each immunization the volunteers have to remain in the clinic for a 30 minutes period for the assessment of local and systemic reactions.
 
The volunteers themselves have to fill an adverse event report form (diary card) for a 4 day observation period after each vaccination. Health status will be checked before each immunization, and on days 21 (+5) 85 (+2) and 204 (+2).
 
Standard blood chemistry and hematology will be assessed at the screening visit (days -7 to -5), prior to each vaccination as well as 7 (+2) and 21 (+5) days after each vaccination.
 |                     |                                                                                                                                                          |                 |                                          |

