| Examination                                                             | Medical history in-/exclusion criteria pregnancy test (women) written informed consent | Assessment of health status (pre-vaccination)                                                                                         |                                                                                      |                                           | Assessment of health status                        | Assessment of health status (pre-vaccination)                                                                                           |                                                                                      |                                           | Assessment of health status                        |                                                                                                                                           |                                                                                      |                                           | Assessment of health status                        |
| Vaccination                                                             |                                                                                        | 0.5 mL i.m. (left)                                                                                                                    |                                                                                      |                                           |                                                    | 0.5 mL i.m. (right)                                                                                                                     |                                                                                      |                                           |                                                    | 0.5 mL i.m. (left)                                                                                                                        |                                                                                      |                                           |                                                    |

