| Blood Sampling T-cell response                              | 25 mL EDTA blood, to be sent to STI within 4 hours                                     |                                                                                                                                       |                                                                                      |                                           | 25 mL EDTA blood, to be sent to STI within 4 hours |                                                                                                                                         |                                                                                      |                                           | 25 mL EDTA blood, to be sent to STI within 4 hours |                                                                                                                                           |                                                                                      |                                           | 25 mL EDTA blood, to be sent to STI within 4 hours |
| Adverse Events (Interviews and diary card)                              |                                                                                        | Baseline AE rate (prior to vaccination) after vaccination 30 minutes observation distribution diary card (self-assessment days 1 – 4) | Picture of injection site, if visible reaction. Recording of AEs check of diary card | Recording of AEs Collection of diary card |                                                    | Baseline AE rate (prior to vaccination) after vaccination 30 minutes observation distribution diary card (self-assessment days 61 – 64) | Picture of injection site, if visible reaction. Recording of AEs check of diary card | Recording of AEs Collection of diary card |                                                    | Baseline AE rate (prior to vaccination) after vaccination 30 minutes observation distribution diary card (self-assessment days 181 – 184) | Picture of injection site, if visible reaction. Recording of AEs check of diary card | Recording of AEs Collection of diary card |                                                    |

 hematology includes: hemoglobin, hematocrite, RBC count, WBC count and differential, platelets count

 blood chemistry includes ASAT/ALAT, alk. Phosphatase, creatinine, CRP

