## 8.2 Surveillance period for occurrence of adverse events

All adverse events occurring within one month (minimum 30 days) following administration of each dose of vaccine/ placebo must be recorded on the Adverse Event Form in the subject's CRF, irrespective of severity or whether or not they are considered vaccination-related.

Additionally, all serious adverse events brought to the attention of the investigator during the period starting from the day of performance of the first study procedure for each subject and ending not earlier than six months (minimum 180 days) following administration of the last dose of study vaccine for that subject must be recorded. See 8.8 for instructions for recording and reporting of serious adverse events.

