### 8.3 Recording adverse events

At each visit/assessment, all adverse events either observed by the investigator or one of his clinical collaborators or reported by the subject spontaneously or in response to a direct question will be evaluated by the investigator. Adverse events not previously documented in the diary card will be recorded in the Adverse Event form within the subjects CRF. The nature of each event, date and time (where appropriate) of onset, outcome, intensity and relationship to vaccination should be established. Details of any symptomatic/corrective treatment should be recorded on the appropriate page of the CRF.

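### The Schedule, 5.2.3, the synopsis and the Flow Chart leave adverse event recording out of the 21 (+5) day visit, which contradicts the 30-day and every-visit rules of section 8

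*Protocol*

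**What the plan says.** **Visit-level text.**
- Protocol 5.2.3 asks for AE recording at the first and second follow-up visits. For the third it gives a different list: "The investigator has to assess the health status of the participant and to take blood samples for safety and immunology tests".
- The AE row of the Schedule of Assessments has its last entry per dose at the 7 (+2) day visit: "Recording of AEs Collection of diary card". The cells at study days 22-27, 78-96 and 197-213 are empty.
- The synopsis safety criteria, besides a 4-day diary, give "assessment by investigator during 30 minutes after each vaccination and 2 (+1) days as well as 7 (+2) days after each vaccination". The synopsis procedure places safety assessments before each dose "as well as 2 (+1) and 7 (+2) days after each immunization".
- The Flow Chart names an interview plus laboratory tests at the 7-day visit, but only laboratory tests and immunology at the 21-day visit. This holds in every cohort and after every dose.

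**Section 8.**
- 8.2: "All adverse events occurring within one month (minimum 30 days) following administration of each dose of vaccine/ placebo must be recorded"; 8.7 repeats the rule.
- 8.3 begins "At each visit/assessment, all adverse events either observed by the investigator" and goes on to include events volunteered or elicited by asking; 8.7 repeats this, and 8.1 also refers to every study visit.
- 8.3.1 supplies a non-leading question covering the time since the previous visit.

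**Health status.** The synopsis procedure says "Health status will be checked before each immunization, and on days 21 (+5) 85 (+2) and 204 (+2". The Examination row of the Schedule has an entry "Assessment of health status (pre-vaccination" at doses 1 and 2 and nothing at dose 3.

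**The concern.** The occurrence of AEs is the primary safety endpoint (10.2). Section 8 sets a window of at least 30 days per dose, and a visit takes place inside that window at 21 (+5) days. Yet each passage that tells the site what to do at that visit leaves AE recording out. Two other passages push the reader towards the deficient text: 5.2 refers the site to the Schedule for visits and checks, and 10.7.1 ties the safety evaluation to the intervals in the Schedule.

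A site that builds its visit worksheets from the Schedule could draw blood at day 21 without recording what has happened since day 7 to 9. Later non-serious events would then be captured late, from memory, or not at all. That matters for two things the protocol relies on: the AE incidence itself, and the trigger in 9.4 for setting up a DSMB, which counts severe events within a dose and antigen cohort.

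**Working it through.** **Inputs**
- Required window: at least 30 days after each dose (8.2, 8.7).
- Dose days: 1, 57-66, 176-187 (Schedule).
- Last scheduled AE recording: 7 (+2) days after each dose, i.e. day 7 to 9 (Schedule, synopsis, 5.2.3).
- Third follow-up visit: 21 (+5) days after each dose, i.e. day 21 to 26 (Schedule, synopsis).
- AE check before each dose (5.2.2 and the Schedule).

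**Reproducing the plan's own window for the last visit.** Earliest: 176 + 21 = 197. Latest: 187 + 26 = 213. This matches the stated 197-213.

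**Reading 1: the site works from the Schedule.** Days after the last scheduled AE recording = 30 − last contact day.
- 30 − 7 = 23, and 23/30 = 77%.
- 30 − 9 = 21, and 21/30 = 70%.

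The wait until the next scheduled AE question, from the 7-day visit to the next pre-dose check, is:
- After dose 1 (days 8-10 to 57-66): 57 − 10 = 47 to 66 − 8 = 58 days.
- After dose 2 (days 64-75 to 176-187): 176 − 75 = 101 to 187 − 64 = 123 days.
- After dose 3: there is no further scheduled question.

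**Reading 2: the site follows section 8.** AEs are also evaluated at the third follow-up visit.
- 30 − 21 = 9, and 9/30 = 30%.
- 30 − 26 = 4, and 4/30 = 13%.

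After dose 1 the next pre-dose check falls 57 − 1 = 56 to 66 − 1 = 65 days after the dose. After dose 2 it falls at least 176 − 66 = 110 days after. Both are past day 30, so the remainder is asked about, though late. After dose 3 the window ends on day 176 + 30 = 206 to 187 + 30 = 217, the last visit is on day 197 to 213, and no visit covers the final 4 to 9 days.

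5.2.3 gives 22 (+5) where the Schedule and synopsis give 21 (+5). With 22 (+5) the remainder is 30 − 27 = 3 to 30 − 22 = 8 days, so the conclusion does not change.

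**Escalation under Reading 1 (Flow Chart).** Groups C and D start in study week 6. The next AE entry for A and B after their week-2 interview is at dose 2 in week 10. Group E starts in week 20. The next AE entry for C and D after their week-16 interview is at dose 3 in week 32. On this reading, later non-serious events in the preceding cohort have no scheduled recording before the next cohort begins.

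**The case against.** The strongest reply is that the design already asks about AEs at day 21. 8.1, 8.3 and 8.7 apply to every visit, the question in 8.3.1 reaches back to the previous visit, and the opening of section 8 makes the investigator responsible for documenting all AEs under that section's guidelines. On that view an empty cell is an omission in a summary table and cancels no duty. The 21-day visit also has a health-status assessment and safety laboratory tests, volunteers are asked about medication at each visit (5.4, 6.8), and they are told to report anything they perceive as serious.

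Much of this stands. A reader might infer that most of each window is never asked about, or that everything late after dose 3 is lost. The document does not support that: it is true only if section 8 is set aside. A reader might also infer that a falling AE rate by dose 3 would be an artefact of less asking. All groups share one schedule, 10.6 compares groups on presence or absence of an event per person, and no comparison by injection number is stated, so no planned analysis is shown to be affected.

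What the reply does not remove is the contradiction. It is not one missing cell: the prose of 5.2.3, two synopsis passages and the Flow Chart all agree with the blank cells. Nor does the health-status check stand in for AE recording, because the synopsis lists a reduction in health status as a criterion separate from the occurrence of AEs.

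**Conclusion.** The point holds as a contradiction within the protocol about how the primary safety endpoint is captured, and it should be corrected. It affects 3 of the 9 post-dose follow-up visits for all 46 planned volunteers. Under the Schedule, 21 to 23 of 30 days (70% to 77%) per dose follow the last scheduled AE recording, with none beyond day 7 to 9 after dose 3. Under section 8 the remainder is 4 to 9 days, left without a visit only after dose 3. The document does not say which text prevails, so the effect in practice lies between these two, depending on which text the site follows.

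The finding assumes that the empty cells in the AE row are truly empty; the matching prose and Flow Chart support this. The empty dose-3 cell in the Examination row is less certain, since tables may have been damaged in reading and the synopsis procedure states a check before each dose. It is a smaller, separate inconsistency.

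**What to change.** Make the visit-level text match section 8:
- **Schedule of Assessments:** enter AE recording in the AE row at days 22-27, 78-96 and 197-213.
- **5.2.3:** add recording of AEs since the last visit to the third follow-up visit.
- **Synopsis:** add the 21 (+5) day visit to the investigator's AE assessments in the safety criteria and in the procedure.
- **Flow Chart:** add the interview at the 21-day visits.

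Separately, reconcile the Schedule and the synopsis on the health-status check before dose 3.

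The cost is protocol wording and an AE field in the CRF at three visits that already take place; no visit or procedure is added. It cannot be left to the analysis stage, because events not recorded cannot be recovered then. The change does not close the 4 to 9 days after the last visit following dose 3, where no contact is scheduled at or after day 30.
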